#### Treatment stage

2.6.2

Level of pain, presence of dysfunction, quality of life, and satisfaction level will be examined when hospitalized, 14 days after hospitalization, and during discharge (Table 1)

**Table 1 T1:**
[figure not shown]
Items to be observed by timepoints.

The items to be surveyed are as follows.

-NRS of waist and legs-Quality of life: EuroQol-5D-5L (EQ-5D-5L)-Oswestry Disability Index (ODI)-Physical examination-Adverse effects are examined daily by the medical staff during hospitalization-All records of medical treatments, both western and Korean, performed during hospitalization of the patients

#### Follow-up

2.6.3

Follow-up assessment will be conducted from the baseline of the treatment to 6 months after the treatment. Follow-up via phone call will assess NRS of waist and legs, EQ-5D-5L, ODI, and Patient Global Impression of Change .

### Adverse events

2.7

Adverse events (AEs) are undesirable and unintentional signs (ie, abnormal laboratory test result), symptoms, or disease. The researchers will analyze the frequency of AEs, abnormal blood test results, and severe adverse events. During the inpatient treatment period and telephone follow-up, the researchers will confirm and analyze the presence of AEs.

The staff will determine and record the treatments that are likely responsible for the AEs that have occurred and will evaluate the causal relationship between each treatment method and AEs in a six-stage scale (1 = definitely related, 2 = probably related, 3 = possibly related, 4 = probably not related, 5 = definitely not related, and 6 = unknown).

All AEs will be classified into the following 3 levels by Spilker classification^[12]^:

Mild: When no treatment is required and the side effect does not significantly impair the normal life (function) of the subject; Moderate: When the side effect significantly impairs the normal life (function) of the subject, may require treatment, and can recover after treatment, and Severe: When severe adverse reactions require advanced treatment and may have after effects).

### Withdrawal and dropout criteria

2.8

At any time during the study, the subject may voluntarily withdraw from the study or be dropped out at the researcher's discretion. If the clinical study is discontinued for the subject, the investigator will assess and record the main cause of the dropout.

1)Patients who have been hospitalized for ≤7 days2)Patients whose guardian or they themselves requests to be withdrawn from the study during the study period or subject withdrawal of consent to participate in the clinical research3)When progress of the research is deemed unsuitable by other investigators4)If the patient is not applicable in at least 1 “selection criterion"5)If the patient is not applicable in at least 1 “exclusion criterion"6)Subjects whose systematic disease was not found in the pre-clinical examination7)If the subject cannot participate in follow-up

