#### Screening process

2.6.1

Participants will be screened using the inclusion/exclusion criteria. MRI imaging and analysis will be performed to confirm LDH. The pain level needs to be checked for the presence of radiating pain per inclusion criteria. Only MRIs taken within the last 3 years will be accepted, and only after confirming that MRI and lower extremity radiating pain meets inclusion criteria will the patients be enrolled in the study. The type and the location of intervertebral herniation in the lumbar spine will also be recorded.

-Whether or not desiccated disc change is accompanied in each level and whether bulging disc is accompanied-Whether or not extrusion, protrusion, bulging, sequestration, and migration is accompanied in each level-In case of extrusion or protrusion, confirm the following: central zone, Lt. subarticular zone, Rt. Subarticular zone,—both subarticular zone, left foraminal zone, Rt. foraminal zone, both foraminal zone, Lt. extraforaminal zone, Rt. extraforaminal zone, and both extraforaminal zone-In case of sequestration/migration, confirm the following: sequestration, inferior migration, and superior migration

To determine whether the patient has spinal stenosis, MRI will confirm the presence of spinal stenosis and neurogenic claudication. Radiological criteria for spinal stenosis may include those that meet the criteria under MRI or those that have been identified by a radiologist. Additionally, the level and type of stenosis will be recorded. Types of stenosis to be recorded are: central, foraminal, and central and foraminal.

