### Statistical analysis

2.10

In this study, intention-to-treat will be the primary analysis. In case of missing values, among multiple imputation, Markov Chain Monte Carlo, and Last observation carried forward will be implemented. Additionally, differences between the baseline and the following timepoints will be tested using paired *t* test or Wilcoxon signed rank test, and differences in time by treatment interactions will be subjected to repeated measures of analysis of variance; if necessary, linear mixed model analysis will also be conducted. Continuous variables are presented as mean (standard deviation) or median (quartile), and categorical variables are expressed in frequency (%) and will be subjected to *χ*^2^ test or Fisher exact test. All statistical analyses were performed by SAS version 9.1.3 statistical package (SAS Institute, Cary, NC) and *P* < .05 was considered statistically significant.

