Another limitation is that 1000 patients may be large in recruitment but lack safety aspects; during hospitalization, systematic investigation will be conducted with Korean medical doctors investigating and recording the side effects on a daily basis, but in terms of safety, it can be a small number to collect rare events. However, if the system is established and the registry research is expanded through this study, it can serve as a foundation to accumulate safety data in the future.

Additionally, it is expected that there will be many dropouts, as the protocol is configured so that many people with <7 days of inpatient treatment will be withdrawn or drop out. In reality, some patients are admitted for examination and treatment just for insurance benefits if private insurance only supports those with hospitalization, and those with severe initial pain and movement restrictions may improve quickly and will be hospitalized and discharged in a short time. In these cases, hospital stays tend to be shorter. Although we tried to establish a registry to properly validate the efficacy of Korean medicine treatment and exclude inpatients from the test, there may be possibilities where the rate of dropouts is high or the information about the late adverse events in dropout patients is missing. We plan on thoroughly reviewing the reasons for dropouts and revisit those patients with adverse effects during hospitalization.

The strength of this study is that it seeks to recruit many patients, as many as 1000. It is also the first study to prospectively recruit those going through CAM inpatient treatment to examine its efficacy and safety in many people. We will not only confirm the safety and efficacy of integrative Korean medicine treatment in 1000 LDH patients but also analyze whether the individual characteristics such as presence of stenosis, sex, age, and type of disc hernia can affect the treatment. This study is expected to not only provide the basis for validating CAM treatment but to also establish the basis for safety, which has been lacking in the past.

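### A stay of 7 days or less is a withdrawal reason applied after enrolment; this is not reconciled with the intention-to-treat primary analysis and is partly outcome-related

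*Protocol article*

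**What the plan says.** Under Screening process (2.6.1), "only after confirming that MRI and lower extremity radiating pain meets inclusion criteria will the patients be enrolled in the study". Length of stay appears in neither the inclusion nor the exclusion criteria (2.5).

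Withdrawal and dropout criteria (2.8) then begins with "Patients who have been hospitalized for ≤7 days".

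Statistical analysis (2.10) states: "In this study, intention-to-treat will be the primary analysis". On missing data it adds: "In case of missing values, among multiple imputation, Markov Chain Monte Carlo, and Last observation carried forward will be implemented". It does not say how patients withdrawn for a short stay are handled.

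The Discussion expects many dropouts because "the protocol is configured so that many people with <7 days of inpatient treatment will be withdrawn or drop out". It gives two causes of short stay. One is admission driven by private insurance cover. The other is clinical: "those with severe initial pain and movement restrictions may improve quickly and will be hospitalized and discharged in a short time". In a loosely worded sentence it presents leaving such inpatients out as part of validating efficacy properly. It accepts that dropout may be high and that late adverse events in dropouts may go unrecorded. Its response is to review the reasons for dropout and to "revisit those patients with adverse effects during hospitalization".

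**The concern.** Intention-to-treat in a single-arm registry can only mean that everyone who entered is analysed, whatever happened afterwards. A rule that withdraws enrolled patients because of a later event pulls against that. Here the event is partly a result of response, since the authors themselves say that some patients leave early because they improve quickly.

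Both parts of the primary objective are exposed. For efficacy, the mean change could describe only patients who needed, or chose, more than a week in hospital. For safety, events that first appear after discharge could be lost in the same patients, because withdrawal may mean that nobody telephones them at 6 months. Follow-up that is never collected cannot be recovered at the analysis stage.

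**Working it through.** The protocol gives no figure for this point: no expected short-stay share, and no derivation of the 1000. There is nothing to reproduce, so the check is first one of logic and then an illustration on stated assumptions.

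**Order of events.** Eligibility is confirmed, the patient is enrolled, the admission assessment is taken and treatment starts. Only later is it known whether the stay was 7 days or less. The rule therefore acts on patients who already have baseline data.

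**Two readings of withdrawal.**

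1. *Short-stay patients leave the analysis set.* The Discussion's wording about leaving such inpatients out favours this reading. The primary analysis is then restricted to those staying longer than a week, and is not intention-to-treat.
2. *They stay in the set, but participation ends.* The label then holds, but the rule itself stops collection. The 6-month values, and possibly the discharge values, are missing by design and must be imputed or carried forward. If the admission value is the last one held, carrying it forward sets the patient's change to zero, including for someone discharged because of quick improvement. The in-hospital 2-week assessment is a separate matter: anyone discharged before day 14 has left by then, with or without this rule.

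**Illustrative size under reading 1.** Let p be the share staying 7 days or less, and let m_S and m_L be the mean improvements in short and long stayers.

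- All-enrolled mean = (1 − p) × m_L + p × m_S
- Retained-only mean = m_L
- Retained-only minus all-enrolled = p × (m_L − m_S)

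With d as the absolute difference between m_L and m_S, the shift has size p × d. Both inputs are assumptions; the protocol says only that such patients will be many.

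| Assumed p | Retained of 1000 | Shift, d = 1 NRS point | Shift, d = 2 NRS points |
|---|---|---|---|
| 10% | 900 | 0.1 | 0.2 |
| 20% | 800 | 0.2 | 0.4 |
| 30% | 700 | 0.3 | 0.6 |
| 40% | 600 | 0.4 | 0.8 |

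**Sign.** If short stayers improve more (m_S > m_L), which is the mechanism the Discussion names, the retained-only mean understates improvement. If some leave early through lack of benefit or harm, it overstates improvement, but the protocol does not name that cause. Insurance-motivated stays have no clear direction.

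**Safety.** Adverse events are examined daily in hospital (2.6.2) and again at telephone follow-up (2.7). A short-stay patient contributes the first source but, once withdrawn, may not contribute the second. The planned revisit covers those who already had an event in hospital, and so does not reach a patient whose first event comes after discharge.

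**Cut-off.** Section 2.8 uses ≤7 days and the Discussion <7 days. They differ only for a stay of exactly 7 days.

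**The case against.** The strongest reply is that section 2.8 governs participation, not analysis sets. It does not say that collected data are discarded. Section 2.10 provides for missing values, and the definition of analysis sets may sit in a full protocol or SAP that is not shown. A reader might infer a flat contradiction with intention-to-treat; the text does not establish that, because the second reading is formally compatible with it. What stands is that the two rules are not reconciled, that the Discussion points towards exclusion, and that on either reading the rule costs outcome data which could have been collected.

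A reader might also infer that the adverse event rate will describe only patients who stayed more than a week, or that precision for rare events falls with the retained number. The document does not support this. Daily in-hospital recording covers short stayers too, and only late events are conceded as possibly missing.

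A reader might suspect that the rule flatters the treatment. The only outcome-related cause named works the other way; early discharge for dissatisfaction or harm is plausible but is inference.

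The authors also disclose the loss, give a rationale for the rule, record the main cause of each dropout, and plan to review those causes. That is fair, but disclosure does not settle who is in the primary analysis. The ≤7 versus <7 difference is minor, since every stay under 7 days also meets the ≤7-day rule.

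**Conclusion.** The concern holds in this form: a withdrawal criterion known only after enrolment, and by the authors' own account partly driven by quick improvement, is not reconciled with an intention-to-treat primary analysis. Exclusion makes the analysis a selected one; retention makes the later outcomes missing by design. The loss is avoidable, because it follows from the rule and not from the patients.

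The size is not computable from the document. The range of 0.1-0.8 NRS points applies only if short stayers are excluded, and it rests on an assumed share of 10-40% and an assumed difference of 1-2 points. The net direction is unknown. For safety, the gap is confined to late events in short-stay patients.

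**What to change.** - Remove the stay of 7 days or less from the withdrawal reasons in 2.8.
- Keep every consenting, eligible patient with an admission assessment in the primary and safety sets.
- Take the existing discharge assessment whenever discharge occurs, and make the existing 6-month telephone contact, including the adverse event question, for all of these patients.
- Report patients staying longer than the cut-off as a supplementary set, using one cut-off throughout (reconcile ≤7 and <7 days).
- State that withdrawal under criteria 3 (investigator judgement) and 7 (unable to take part in follow-up) ends further collection but does not remove data already collected.

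If the sponsor prefers a minimum-stay population as primary, naming it as such and dropping the intention-to-treat label would remove the inconsistency of wording, but not the selection or the missing late follow-up.

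The cost is a change of wording plus one discharge form and one telephone call per short-stay patient, both of which are existing procedures. The mean effect may move in either direction.

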### Data management

2.9

An investigator from the coordinating center will distribute a standard operating procedure (SOP) to be used in study processes such as Case Report Form (CRF) completion and data input, and will provide instruction for assessor and investigators at each center. CRF data will use double data entry, and data entry will be performed by each participating center and the coordinating center. After cross-checking the input data, access to the data will be blocked from all investigators except the data coordinator.

### Statistical analysis

2.10

In this study, intention-to-treat will be the primary analysis. In case of missing values, among multiple imputation, Markov Chain Monte Carlo, and Last observation carried forward will be implemented. Additionally, differences between the baseline and the following timepoints will be tested using paired *t* test or Wilcoxon signed rank test, and differences in time by treatment interactions will be subjected to repeated measures of analysis of variance; if necessary, linear mixed model analysis will also be conducted. Continuous variables are presented as mean (standard deviation) or median (quartile), and categorical variables are expressed in frequency (%) and will be subjected to *χ*^2^ test or Fisher exact test. All statistical analyses were performed by SAS version 9.1.3 statistical package (SAS Institute, Cary, NC) and *P* < .05 was considered statistically significant.

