#### Protocol overview

2.1.1

This study is a prospective observational study having a registry and no control group. All treatments during hospitalization will be recorded with no restrictions. We plan on recruiting 1000 patients admitted at 4 spine specialized Korean medical hospitals. Patients enrolled in the registry will be evaluated on predefined outcome variables (pain, quality of life, disability, and physical examination) at the time of hospitalization, 2 weeks after hospitalization, at discharge, and 6 months after hospitalization. The protocol of this study was registered in CRIS (KCT0003709) and Clinical trial gov (NCT03750591).

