## Discussion

3

Our study aimed to establish a prospective registry of 1000 patients to overcome the limitations of Korean integrative medicine or CAM-related research, which involved a small number of patients or a large number of retrospective patients, and to confirm the safety and efficacy of Korean medicine treatment for lumbar disc herniation. Additionally, the effect of the treatment was not only observed immediately after the treatment, but also 6 months after, to analyze the long-term treatment effect of Korean medicine treatment for LDH, which is common in recurrence of chronic pain. Also, as a large number of patients were recruited, we can analyze whether the treatment effect differed among CAM inpatient and whether individual characteristics such as age, sex, and presence of stenosis and accompanying diseases influenced the time of improvement. This study was designed as the first project of the Joint and Spine Pain Integrative Evaluation registry (J-SPINE) project, and in the future, we plan to build a registry for other spinal and joint diseases.

However, the limitation of this study is that it will be conducted without a control group. Although the data on safety can be collected in large numbers, those on effectiveness may be limited due to the absence of the comparison group. However, we plan on recruiting outpatient patients or patients receiving nonintegrated Korean medicine treatment through other registry studies. Through this, it will be possible to check whether inpatient Korean medicine treatment is more effective than the outpatient treatment and on which patients it would be more effective towards. Moreover, if the analysis is carried out according to whether there is a difference in the effects depending on the presence of stenosis and whether the treatment was accompanied with Western medical conservative treatment (eg, analgesic drug treatment, electrophysical treatment, and so on), it is possible to analyze the advantages of combination treatment even without the control group. Additionally, we can analyze whether there is a difference in treatment effects according to age or sex.

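### LOCF is planned beside MCMC multiple imputation with neither made primary; if it produces the reported 6-month result, it fills in the answer by assumption for patients lost to follow-up

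*Protocol article*

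**What the plan says.** The Statistical analysis section (2.10) states that "intention-to-treat will be the primary analysis" and that, for missing values, "among multiple imputation, Markov Chain Monte Carlo, and Last observation carried forward will be implemented". Change from baseline is tested by paired tests, followed by repeated-measures ANOVA. A linear mixed model is added only if needed.

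The Protocol overview (2.1.1) describes a registry without a control group, with assessments "at the time of hospitalization, 2 weeks after hospitalization, at discharge, and 6 months after hospitalization". The Discussion gives the purpose of the last visit: "to analyze the long-term treatment effect of Korean medicine treatment for LDH, which is common in recurrence of chronic pain". It also warns that "it is expected that there will be many dropouts", mainly because of short stays.

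The Withdrawal and dropout criteria (2.8) include "Patients who have been hospitalized for ≤7 days" as criterion 1 and "If the subject cannot participate in follow-up" as criterion 7.

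**The concern.** Multiple imputation and LOCF rest on different assumptions and can give different 6-month results. As the sentence stands, either could be reported as the main result once the data are seen.

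LOCF is the weaker of the two here, for three reasons.

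- **Patients lost between discharge and 6 months.** LOCF repeats a score taken at the end of inpatient care. It therefore assumes that nothing changed afterwards, which is the question the 6-month visit is there to answer.
- **Patients who leave early with only an admission score.** LOCF assigns zero improvement. The Discussion says that some short-stay patients improve quickly, so this can err the other way.
- **Copied values count as observed.** The standard error is computed as if every patient had been measured at 6 months.

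In a two-arm trial, part of such an error might cancel between arms. Here the estimate is a within-patient change in a single group, so the whole error stays in it.

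**Working it through.** The protocol gives no dropout rate, relapse rate, SD or effect size, so there is no figure of its own to reproduce. What follows shows how the error behaves under stated assumptions.

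**Inputs**

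- From the protocol: N = 1000, no control arm, four assessment times, within-patient change.
- Assumed: mean improvement at discharge 3 NRS points; SD of change 2; correlation 0.5 between the changes at discharge and at 6 months; share lost after discharge m6 = 0.2 or 0.3; mean loss of benefit from discharge to 6 months r = 0 to 1 point; share with an admission score only m0 = 0 to 0.2; losses unrelated to the scores.

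**Bias of LOCF.** Let G = 3 − r be the true mean improvement at 6 months. The LOCF mean is

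(1 − m6 − m0)·G + m6·(G + r) + m0·0 = G + m6·r − m0·G,

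so bias = m6·r − m0·G. A positive value overstates improvement.

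| m6 | r | m0 | Bias (NRS points) |
|---|---|---|---|
| 0.2 | 0 | 0 | 0 |
| 0.2 | 0.5 | 0 | 0.2 × 0.5 = +0.10 |
| 0.2 | 1 | 0 | 0.2 × 1 = +0.20 |
| 0.3 | 0.5 | 0 | 0.3 × 0.5 = +0.15 |
| 0.3 | 1 | 0 | 0.3 × 1 = +0.30 |
| 0.2 | 1 | 0.1 | 0.20 − 0.1 × 2 = 0 |
| 0.2 | 1 | 0.2 | 0.20 − 0.2 × 2 = −0.20 |
| 0.2 | 0.5 | 0.1 | 0.10 − 0.1 × 2.5 = −0.15 |

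The sign changes at m0 = m6·r/G. With m6 = 0.2 that is 0.2 × 1/2 = 0.10 at r = 1, and 0.2 × 0.5/2.5 = 0.04 at r = 0.5. A small group of admission-only dropouts is enough to reverse the direction.

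**Interval width, losses after discharge only.** LOCF uses all 1000 values as if measured: 2 × 1.96 × 2/√1000 = 0.248. Imputation from the discharge score has approximate variance 4 × [0.25/1000 + 0.75/(1000(1 − m6))].

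- m6 = 0.2: 4 × (0.00025 + 0.00094) = 0.00475, width 0.270. LOCF is about 8% narrower.
- m6 = 0.3: 4 × (0.00025 + 0.00107) = 0.00529, width 0.285. LOCF is about 13% narrower.

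A simulation (500 runs, 10 imputations) agrees: LOCF width 0.247-0.254 against 0.271-0.273 at m6 = 0.2 and 0.289-0.290 at m6 = 0.3. LOCF is thus 7-9% and 12-14% narrower.

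**Coverage of the nominal 95% interval, same simulation, m0 = 0**

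| m6 | r | LOCF | Multiple imputation |
|---|---|---|---|
| 0.2 | 0 | 94% | 94% |
| 0.2 | 0.5 | 66% | 95% |
| 0.2 | 1 | 12% | 94% |
| 0.3 | 0 | 94% | 95% |
| 0.3 | 1 | under 1% | 95% |

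Bias of multiple imputation was at most 0.004 in these rows. Where there is no drift, LOCF coverage holds despite the narrower interval, so the damage comes mainly from bias. At N = 1000 the interval is narrow enough for a bias of 0.1-0.3 points to matter.

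**The case against.** The strongest reply has five parts.

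1. **LOCF is not the only method named, and an SAP may rank them.** This stands in part. A reader might infer that the 6-month result is biased as planned. The text does not support that: the bias reaches the reported result only if LOCF produces it. A missing ranking alone could be left to an SAP. Naming LOCF as a method to be used is a stated choice, and that can be criticised here.

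2. **The protocol does not say that mean pain rises after discharge.** This stands. Common recurrence in some patients is compatible with a stable mean, no rate is given, and the Introduction reports that earlier follow-up found the effect maintained. A reader might infer that LOCF flatly contradicts the protocol's premise, but the drift r is an assumption. Even so, the visit exists to test maintenance, and LOCF assumes it for those not reached.

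3. **The direction is not settled.** This stands. A reader might infer bias towards benefit only. Admission-only dropouts push the other way. Their share is unknown, because a discharge assessment is scheduled and some early leavers may have one.

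4. **The narrowing is easily overstated.** This stands. The factor √(1 − m), which gives 0.89 at 20% and 0.77 at 40% missing, compares LOCF with a complete-case analysis. Multiple imputation recovers information from the discharge score, so the gap is smaller.

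5. **Criterion 7 is a separate matter.** This stands. A reader might infer that patients who cannot be followed up are deleted. Section 2.8 lists reasons for dropout and does not say that their data are removed; under intention-to-treat they would stay in as missing data.

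**Conclusion.** The point holds in conditional form. LOCF is a stated method in a single-arm study that expects many dropouts, and no method is made primary. If LOCF is used for the reported result, it assumes a maintained effect for patients lost after discharge and no effect for those with an admission score only.

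For losses after discharge alone, at 20-30% lost and a mean relapse of 0.5-1 point, the overstatement is 0.10-0.30 NRS points with intervals 7-14% too narrow relative to multiple imputation. It is zero without mean drift, and it can vanish or turn negative once admission-only dropouts are added. All these rates are assumptions. The good performance of multiple imputation was shown for losses unrelated to the scores; it does not protect against losses that depend on the unseen 6-month score. The sign of the net error cannot be stated from the document, which is itself a reason not to rest the 6-month result on LOCF. The change should be made before the data are analysed.

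**What to change.** - **Primary analysis.** Choose one: multiple imputation by MCMC, with admission, 2-week and discharge scores, length of stay, age, sex, stenosis and centre in the imputation model; or a linear mixed model on all observed visits. The two are similar but not equivalent unless the mixed model carries the same auxiliary variables.
- **LOCF.** Remove it, or confine it to an analysis labelled as sensitivity.
- **Sensitivity.** Add delta-adjusted imputation in which patients not reached at 6 months are taken to be worse than imputed, for example by 0.5, 1 and 2 NRS points.
- **Criterion 7.** State that patients who meet it stay in the intention-to-treat set, with their 6-month values treated as missing.

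The cost is wording and minor programming. Intervals become slightly wider, and the 6-month figure may be less favourable.

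### The planned time-by-treatment interaction has no defined treatment factor in a single-cohort registry, so it cannot be estimated as written; a prespecified time effect should replace it

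*Protocol article*

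**What the plan says.** The Protocol overview (2.1.1) of the protocol article describes the design: "This study is a prospective observational study having a registry and no control group". On treatment it says: "All treatments during hospitalization will be recorded with no restrictions". The planned size is 1000 patients from four hospitals, assessed "at the time of hospitalization, 2 weeks after hospitalization, at discharge, and 6 months after hospitalization".

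The Statistical analysis section (2.10) then lists three longitudinal methods in a single sentence:

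- Change from baseline: "differences between the baseline and the following timepoints will be tested using paired *t* test or Wilcoxon signed rank test".
- Interaction: "differences in time by treatment interactions will be subjected to repeated measures of analysis of variance".
- A conditional model: "if necessary, linear mixed model analysis will also be conducted".

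The section does not say what the treatment factor is, does not rank the three methods, and does not say what would make the mixed model necessary. The Discussion (3) repeats that there is no comparison group and assigns comparison patients to other registry studies. It also notes that one could analyse by stenosis and by Western conservative co-treatment, but does not connect either split to the ANOVA.

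**The concern.** A time-by-treatment interaction asks whether the course over time differs between treatment groups. It needs at least two groups, and this design has one. The sentence reads as if carried over from a comparative trial.

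This is not a detail left to an analysis plan. It is a stated inferential test that the stated design cannot support. Two things are at stake. First, an analyst who follows the text must either drop the test or supply a grouping. Any grouping chosen after the data are seen is an unplanned, non-randomised comparison that could be reported as the planned one. Second, the one named model that suits these data is held back behind an undefined condition, so the choice of longitudinal model is also open to the data.

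**Working it through.** The article gives no power calculation or effect size, so there is no figure of the plan's own to reproduce. The check is whether the interaction exists under the design described.

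**Inputs from the article.** Treatment groups G = 1 (Protocol overview and Discussion). Assessments T = 4: admission, 2 weeks, discharge, 6 months (Protocol overview). Planned N = 1000. P < .05; sidedness is not stated, and two-sided is assumed below.

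**Step 1, degrees of freedom as written.** Interaction df = (G-1)(T-1) = (1-1)(4-1) = 0.

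**Step 2, design matrix.** An intercept and three time indicators have rank 4. Adding a treatment column that equals 1 for everyone and its three products with time gives 8 columns, but the rank stays 4. The interaction adds nothing. This is a property of the fixed effects, so it holds equally for repeated-measures ANOVA and for a mixed model.

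**Step 3, what one cohort does support.** The time effect has T-1 = 3 df. With complete data on 1000 patients the ANOVA error df is (1000-1)(3) = 2997. The paired tests of change from baseline are also available.

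**Step 4, the alternative reading.** If treatment means with or without Western co-treatment, G = 2, interaction df = (2-1)(4-1) = 3, and the 8-column matrix has rank 8. The term can be estimated. To see whether precision is then the problem, take the smallest detectable difference in mean change, in SDs of change: (1.960 + 0.842) × sqrt(1/n1 + 1/n2), for two-sided 0.05 and 80% power. The share co-treated and the number analysed are assumptions, because the article gives neither.

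| Share co-treated (assumed) | 1000 analysed | 500 analysed (assumed) |
|---|---|---|
| 10% | 0.30 SD | 0.42 SD |
| 30% | 0.19 SD | 0.27 SD |
| 50% | 0.18 SD | 0.25 SD |

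Precision would be adequate for modest differences. The difficulty is bias: co-treatment is unrestricted and chosen during the stay, plausibly in response to how the patient is doing, and no adjustment is described.

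**Step 5, visit timing and dropout.** The Withdrawal and dropout criteria (2.8) remove stays of 7 days or fewer, so a stay of 8 to 13 days qualifies. In such a patient discharge comes before the 2-week assessment, and in a longer stay it comes after. The order and spacing of occasions therefore differ between patients, while repeated-measures ANOVA treats them as a common set. The Discussion also expects heavy dropout. These facts, and the four centres, are the grounds for a prespecified mixed model. The 0 df in Step 1 is not, since the mixed model cannot recover the interaction either.

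**The case against.** The strongest reply is that the sentence is loose rather than fatal. Treatments are recorded without restriction, so the treatment received will vary, and the Discussion contemplates a split by Western co-treatment. On that reading the interaction is estimable, and the Discussion admits that conclusions on effectiveness are limited without a comparison group. This stands in part: 0 df applies to the plan as written, and Step 4 shows the alternative. But the Statistical analysis section does not adopt that reading, and the Discussion offers it only conditionally. If it is the intended reading, the exposure and its confounder adjustment still have to be stated.

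Three stronger readings are tempting, and the article does not support them.

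- A reader might infer that the registry has no valid main longitudinal test. No test is named as main, and the paired t and Wilcoxon tests in the same sentence are valid for one cohort.
- A reader might infer that the ANOVA would be run on complete cases only, against the intention-to-treat principle. The same section plans imputation (multiple imputation, MCMC and last observation carried forward are named, in unclear wording), and the article gives no missing-data rate from which a loss could be computed.
- A reader might infer that chi-square and Fisher tests would be misapplied to before-after data. The text says only that "categorical variables are expressed in frequency (%) and will be subjected to" those tests. It does not say which comparisons they serve, and valid between-patient comparisons are planned, for example by stenosis.

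It is also fair to say that simply deleting every interaction would do harm: the Secondary objectives (2.1.3) on stenosis and on prognostic factors need time-by-group terms.

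**Conclusion.** The point holds in a limited form. As written, the time-by-treatment interaction has 0 degrees of freedom and cannot be estimated by either named model. This follows from the article's own design statements and needs no assumed figure. If treatment means Western co-treatment, the term has 3 degrees of freedom but is a confounded observational contrast for which no adjustment is given.

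The tests of change from baseline are unaffected, so the damage is confined to the interaction and to the open choice of longitudinal model. The preference for a mixed model rests on the variable discharge day, the expected dropout and the four centres. The sentence should be corrected before the data are analysed.

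**What to change.** In the Statistical analysis section:

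1. Replace the time-by-treatment interaction and its repeated-measures ANOVA with the time effect, reported as mean change from admission with 95% CI at each assessment.
2. Estimate it from a prespecified linear mixed model that uses all observed visits, with centre (four levels) as a fixed effect. Remove the condition on its use.
3. Deal with the discharge day explicitly: either model actual days since admission, or analyse discharge separately from day 14 and 6 months. Categorical time with discharge as one fixed occasion does not solve the timing problem.
4. Use time-by-group terms only for named observational factors: stenosis and the prognostic factors of the Secondary objectives, and Western co-treatment if wanted. State the confounders adjusted for and label the results as non-causal.

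The paired tests can stay as simple supporting analyses.

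The cost is a change of wording and slightly more analysis work. No new data are needed, and the mixed model is already named. The downside is that the model assumes data missing at random, which should be stated given the dropout expected.
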